# Neural Mechanism of Cognitive Reserve in Acupuncture Stimulation: Protocol for a Randomized, Placebo-Controlled Functional Near-Infrared Spectroscopy Trial

**DOI:** 10.2196/66838

**Published:** 2025-02-19

**Keywords:** cognitive reserve, acupuncture, dementia, mild cognitive impairment, neuroimaging, fNIRS, brain connectivity, neural mechanism, RCT, randomized controlled trial

## Abstract

**Background:**

Dementia is a clinical syndrome characterized by a progressive decline in various cognitive domains. Since there is still no treatment for dementia, early diagnosis and prevention are the best approaches. In this context, the cognitive reserve (CR) concept has received considerable attention in dementia research with regard to prognosis. It originates from discrepancies between the degree of brain pathology and clinical manifestations. Acupuncture, as a complementary intervention, has long been widely applied in neurological diseases in East Asia. At the macroscale level, how acupuncture stimulation affects neural activity concerning CR in normal aging and dementia is largely unknown.

**Objective:**

The aim of this study is to investigate the acute neural mechanisms of acupuncture stimulation concerning CR in the normal aging group and the group with cognitive impairment using neuroimaging methods.

**Methods:**

This study is a randomized, placebo-controlled trial. Participants without (n=30) and with cognitive impairment (n=30) will be randomly assigned to the verum or sham acupuncture groups. The verum acupuncture group will receive acupuncture stimulation at acupoints related to cognitive function and gain deqi sensation. The sham acupuncture group will receive superficial needling at nonacupoints not related to cognitive function. Each group will undergo cognitive function tests, functional near-infrared spectroscopy imaging before and after acupuncture stimulation, and an assessment of CR. The primary outcomes will be differences in resting brain activities according to disease status, differences in resting brain connectivity before and after acupuncture stimulation between the 2 groups, and changes in brain activity in relation to the CR index. The secondary outcomes will be brain connectivity or network metrics associated with CR and differences in neural activity between the cognitive task and resting states.

**Results:**

The recruitment began in August 2023; to date, there have been 50 participants, divided into 20 in the group with cognitive impairment and 30 in the unimpaired group. The recruitment process will continue until February 2025.

**Conclusions:**

CR refers to the individual susceptibility to age-related brain changes and pathologies in cognitive impairment, and it is a factor affecting the trajectories of the disease. Although acupuncture is a widely used intervention for various neurological diseases, including dementia, its mechanism associated with CR at the macroscale has not been clearly identified. This study could contribute to identifying the neural mechanisms of acupuncture stimulation associated with CR using neuroimaging methods and provide a basis for future longitudinal research.

**Trial Registration:**

Clinical Research Information Service of the Republic of Korea KCT0008719; https://tinyurl.com/ydv5537n

**International Registered Report Identifier (IRRID):**

DERR1-10.2196/66838

## Introduction

Cognitive impairment refers to a generic term in which various cognitive functions, such as memory and executive function, are impaired, and the symptom severity ranges from mild to severe enough to interfere with daily life. Among them, dementia is a clinical syndrome preventing patients from leading a daily life due to the severe decline in several cognitive domains. Alzheimer disease (AD) is by far the most frequent cause of dementia and accounts for up to 80% of all dementia diagnoses [1]. AD symptoms typically begin with mild memory difficulties and gradually progress to severe memory impairment, inducing dysfunctions in daily life [2]. The prevalence and incidence of AD are increasing with an increase in life expectancy, leading to a socioeconomic burden worldwide [3,4].

The concept of cognitive reserve (CR) has received consistent attention in dementia-related research. CR refers to the adaptability of cognitive processes, which helps explain the individual vulnerability of cognitive abilities. It has also been suggested as an active model of the reserve, indicating that dynamic cognitive and functional processes counteract aging-related brain changes or damage [5]. This concept suggests that the brain actively attempts to cope with brain damage, allowing an individual with high CR to better deal with brain pathology. Many studies have shown that CR works differently depending on disease status. In the group without cognitive impairment, participants with high CR showed a slower decline in cognitive function; however, in the AD group, individuals with high CR showed more rapid cognitive deterioration than those with low CR [6,7]. Therefore, CR is considered a factor that modulates the relationship between the neuropathological burden of dementia and clinical symptoms [8,9]. Generally, CR has been measured through proxies, such as years of education, occupational complexity, and questionnaires covering various lifelong experiences.

Various neuroimaging techniques such as magnetic resonance imaging, functional magnetic resonance imaging (fMRI), positron emission tomography, and electroencephalography have been used for the early detection of AD [10]. Although fMRI is noninvasive and has good temporal and excellent spatial resolutions among functional neuroimaging methods, it has inherent limitations such as high cost, immobility due to heavy equipment, and vulnerability to head motion artifacts. In contrast, functional near-infrared spectroscopy (fNIRS) has been suggested as an alternative tool for functional neuroimaging. fNIRS is an optical neuroimaging technique that allows the measurement of changes in brain tissue concentrations of oxyhemoglobin (HbO_2_), deoxyhemoglobin (HbR), and total hemoglobin (HbT) within the brain, achieved by irradiating the head with near-infrared (NIR) light [11,12]. This equipment has several practical advantages over conventional techniques represented by fMRI: It has a relatively higher temporal resolution, is noninvasive, cost-effective, lightweight, and easy to handle. It is applicable to cases difficult to fMRI scanning, such as agitated patients, individuals with claustrophobia, and those with pacemakers [13,14]. Moreover, it can be used on patients without moving from the hospital or laboratory, which can be critical for dementia patients with mobility difficulties. With these advantages, it allows us to monitor the alterations in brain function in patients with cognitive impairment in real time and explore neural responses induced by long-term or short-term interventions.

In a recent systematic review of dementia research using fNIRS, its diagnostic and investigative usefulness was evaluated while reviewing 88 studies in the field of dementia [15]. In summary, fNIRS could capture the aberrant hemodynamic responses and a lack of task-appropriate lateralization, often focused on frontal regions, in dementia. On the other hand, inconsistent results were found in prodromal stages. Cognitive decline accompanied by either reduced functional responses or hyperactivity was identified, the latter implying a compensatory response not represented at the dementia stage. However, there have been few fNIRS studies dealing with CR, one of the important factors in cognitive impairment.

Acupuncture has been practiced for thousands of years as an important treatment for a variety of diseases in East Asian medicine [16,17]. It is also being explored in AD research as a complementary and alternative therapy. In a meta-analysis, acupuncture treatment alone showed acceptable efficacy compared to conventional medicine for the management of AD. In addition, in a randomized controlled trial in patients with mild to moderate AD, acupuncture was found to be safe, well tolerated, and effective in improving cognitive function and global clinical status [18]. Specifically, acupuncture has been shown to regulate the release of central neurotransmitters, including acetylcholine and monoamine neurotransmitters [19]. Current neuroimaging studies of acupuncture cover a variety of diseases ranging from pain-related diseases such as chronic low back pain to peripheral and central nervous system disorders including carpal tunnel syndrome, stroke, Parkinson’s disease, and dementia [20-24]. Through these, the analgesic mechanism and neuroprotective effect of acupuncture, which are distinct from sham needling, are consistently elucidated. Among them, a systematic review dealing with 13 AD-related neuroimaging studies found that acupuncture may modulate the default mode network, the central executive, and the frontoparietal networks in the brains of AD patients [24]. However, on the macroscale, the acute neural mechanisms of acupuncture stimulation in relation to CR according to disease status are largely unknown. To identify the neural mechanisms of acupuncture stimulation associated with CR in healthy aging and cognitive impairment patients, rigorous clinical trials such as randomized, placebo-controlled trials with neuroimaging techniques are required.

In this study, our main hypothesis would be that brain networks and brain activations focused on frontal regions would be altered according to the disease status and CR level, and that brain connectivity in the frontal regions would change before and after acupuncture stimulation. Next, we aim to investigate the neural substrates of CR and cognitive function using network metrics. Herein, we present a protocol for a randomized, placebo-controlled, parallel-group clinical trial to explore the acute neural changes after acupuncture stimulation according to CR and elucidate the neural substrates of CR according to disease status by applying fNIRS.

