### Outcome Measures

This study aims to explore the immediate neural mechanisms of the acute response to acupuncture stimulation associated with CR in normal aging and disease status and identify the neural substrates of CR.

The primary outcomes will be as follows: (1) differences in brain activation and resting-state brain connectivity according to disease status (the groups with vs without cognitive impairment); (2) differences in brain activation before and after acupuncture between study and control groups (verum acupuncture vs sham acupuncture); and (3) differences in brain activation according to CR (high CR group vs low CR group).

Secondary outcomes are brain connectivity or network metrics (graph theoretic metrics) associated with the CRIq index, differences in brain activity between working memory tasks and resting states, and network metrics associated with cognitive function scores (MMSE-K, K-MoCA).

The brain connectivity matrix will be obtained as Pearson correlation between 48 channels using time-series data during the scan period (Figure 3). Network metrics, including the index of efficiency, clustering coefficient, and centrality, can be calculated using the connectivity matrix by the Brain Connectivity toolbox in MATLAB 2023b (The Mathworks).

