### Statistical Analysis

Only data from participants who completed the fNIRS scan, cognitive function test, and measurement of CR will be contained in the statistical analysis. All categorical data are presented as frequencies or percentiles and will be analyzed using the chi-square or Fisher’s exact test. All numerical data will be presented as the mean and standard deviation and analyzed using an independent *t* test or Wilcoxon rank-sum test. Preprocessing and analyses of fNIRS data will be performed using MATLAB and the NIRSIT analysis tool.

A two-sample *t* test will be performed to compare the brain activations and connectivity between the groups with and without cognitive impairment. A paired *t* test will be conducted to compare the brain activations and connectivity before and after acupuncture stimulation. The CR values from CRIq will be applied for correlation analysis in the form of continuous variables or divided into binary groups (high and low CR) by mean values for subgroup analysis. Since the expression of CR may appear differently depending on the disease status, a subgroup analysis will be conducted by dividing the healthy control and the patient group. Mixed model analysis will be adjusted to determine the interaction effect of intervention and CR in both groups. Pearson correlation will determine the CR-related brain connectivity or clinical score–related metrics. If there is a significant age difference between 2 groups, the age factor will be added as a covariate in the analysis to adjust the effect of age as much as possible.

Statistical significance in fNIRS imaging would be explored using uncorrected and corrected levels (false discovery rate and family-wise error). At the uncorrected level, uncorrected *P*<.001 will be used, and at the corrected level, *P*<.05 will be applied.

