### Innovations and Limitations

This is the first study to identify the association between CR, an important factor related to the prognosis of dementia, and acupuncture stimulation. The application of the neuroimaging method (fNIRS) can provide new insights into the neural mechanisms of complementary medicine in the field of convergence research. This randomized, controlled trial can contribute to elucidating the genuine neural response to the acupuncture stimulation. However, as a cross-sectional study, it is not possible to identify the long-term effect of acupuncture treatment on cognitive impairments and explore the longitudinal neural mechanism of acupuncture treatment. Additionally, to ensure the reliability of the data, we still further expand the sample size.

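### The acupuncture primary outcome compares verum with sham, but the test named for the before/after data is a within-person paired t test that makes no use of the sham arm

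*Protocol article*

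**What the plan says.** All places are in the Protocol article.

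- **Introduction, main hypothesis.** It has two clauses. The first concerns disease status and CR: "brain networks and brain activations focused on frontal regions would be altered according to the disease status and CR level". The second concerns acupuncture: "brain connectivity in the frontal regions would change before and after acupuncture stimulation". The second does not mention sham.
- **Abstract, Methods.** One primary outcome is "differences in resting brain connectivity before and after acupuncture stimulation between the 2 groups".
- **Outcome Measures, primary outcome 2.** "differences in brain activation before and after acupuncture between study and control groups (verum acupuncture vs sham acupuncture".
- **Statistical Analysis.** For before/after: "A paired *t* test will be conducted to compare the brain activations and connectivity before and after acupuncture stimulation". The two-sample t test on activation and connectivity is assigned to participants with versus without cognitive impairment. The mixed model is aimed at the interaction of intervention with CR. A general sentence gives an independent t test or rank-sum test for numerical data, without linking it to the change between scans. Imaging thresholds are P<.001 uncorrected and P<.05 corrected (false discovery rate and family-wise error).
- **Innovations and Limitations.** The randomised design is cited in support of the expected finding: "This randomized, controlled trial can contribute to elucidating the genuine neural response to the acupuncture stimulation".

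**The concern.** The outcome and the named test have different null hypotheses. The null for primary outcome 2 is that the mean change is the same in verum and sham. The null for the paired t test is that the mean change is zero, whatever the other arm does.

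In both arms the second scan follows a first resting scan, a working memory task and 15 minutes of needling. Practice, fatigue or settling of the sensors could plausibly shift the signal in both arms, although the documents do not discuss this. Such a shift violates the paired null and leaves the between-arm null true.

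Running the paired test arm by arm does not solve this. It invites the conclusion that verum changed and sham did not because one P value fell below the threshold and the other did not, which is not a test of a difference. At stake is whether the randomised comparison decides the acupuncture question it was set up for.

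**Working it through.** **1. Which test goes with which outcome**

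| Contrast | Defined as an outcome in | Imaging test named in Statistical Analysis |
|---|---|---|
| Impaired vs unimpaired | Abstract; primary outcome 1 | Two-sample t test |
| Verum vs sham, before/after change | Abstract (resting connectivity); primary outcome 2 (activation) | None; before/after has a paired t test |
| High vs low CR | Primary outcome 3 | Correlation or subgroup analysis; mixed model for intervention by CR |

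The mixed model does not fill the gap through its stated target. A verum-sham difference that is equal at all CR levels gives an intervention-by-CR interaction of zero, so that term does not test primary outcome 2. An arm-by-time term is not named.

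**2. The plan's own figure**

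Sample Size gives about 10-15 per arm within each disease group at 5% significance and 80% power. No effect size or SD is stated, so the figure can be neither reproduced nor refuted. Solving backwards for a two-sided two-sample comparison, d = (1.960 + 0.842) × √(2/n):

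- n = 10: 2.802 × √0.200 = 1.25
- n = 15: 2.802 × √0.133 = 1.02

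I use n = 15 (one arm within one disease group: 30 participants, 1:1) and n = 30 (one arm with both disease groups combined: 60 participants, 1:1).

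**3. Paired test under a shared change**

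Assumptions: the true verum-sham difference is zero; both arms change by d SDs of the change score, with d = 0.3 or 0.5; change scores are normal. The rejection probability comes from the noncentral t distribution with n − 1 degrees of freedom and noncentrality d√n.

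| n in arm | d | d√n | Critical t, two-sided 5% | Rejects at 5% | Critical t, P<.001 | Rejects at P<.001 |
|---|---|---|---|---|---|---|
| 15 | 0.3 | 1.162 | 2.145 | 19% | 4.140 | 1.0% |
| 15 | 0.5 | 1.936 | 2.145 | 44% | 4.140 | 4.5% |
| 30 | 0.3 | 1.643 | 2.045 | 36% | 3.659 | 3.6% |
| 30 | 0.5 | 2.739 | 2.045 | 75% | 3.659 | 21% |

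With no shared change (d = 0), the rates are 5% and 0.1%. The P<.001 column is per test, for example per channel. At n = 15 it is 10 to 45 times the nominal 0.1%.

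**4. Verum significant, sham not**

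The arms are independent, so the probability is p(1 − p). With 15 per arm and d = 0.5:

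- at 5%: 0.438 × 0.562 = 0.246, about 25%
- at P<.001: 0.045 × 0.955 = 0.043, about 4% per test

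**5. Between-arm test of the change**

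A shared change cancels in the difference. In simulation, a two-sample t test on the change scores rejected in about 5% of trials at the 5% level, and about 0.1% at P<.001, for both arm sizes and both values of d.

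**The case against.** The strongest reply is that the plan already contains the comparison. The Abstract and primary outcome 2 both state it, the design is randomised and placebo-controlled, the general sentence on numerical data allows an independent t test, and a mixed model with intervention would ordinarily carry an arm term. The article also condenses a fuller protocol, and an analysis plan may exist. A sentence in the Introduction does not override a defined outcome.

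Much of this stands, and it limits the point. A reader might infer that the trial ignores its control arm, or that a drift is bound to be reported as an acupuncture effect. The documents support neither. They state the verum-sham outcome, and nowhere say that an acupuncture effect will be claimed from the paired test. Nor is the whole main hypothesis a before/after statement; only its second clause is.

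A reader might also take the 5% rates as the plan's error rates. They are not, because imaging is judged at P<.001 uncorrected or P<.05 corrected, where the rates per test are lower. Whether the paired test is run by arm or on pooled participants is not stated.

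What does not stand is that this is only missing detail. The article names a test for each imaging contrast, and the one it gives to before/after cannot address the stated outcome. The general sentence is not tied to the change between scans, and the model's stated target is a different term.

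**Conclusion.** The point holds as a mismatch. Verum versus sham on the before/after change is a primary outcome, but no imaging test is assigned to it, and the second clause of the main hypothesis leaves out the sham reference. Following the named test as written could give a wrong conclusion if both arms shift together.

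The size depends on a shared change of 0.3 to 0.5 SD, which is assumed, and on the paired test being used for inference. Under those conditions, false attribution in one arm ranges from 19% (n = 15, 0.3 SD) to 75% (n = 30, 0.5 SD) at two-sided 5%. At P<.001 it ranges from 1.0% to 21% per test. With no shared change the excess is nil. Corrected thresholds were not modelled, since they depend on the number of tests and their correlation.

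**What to change.** 1. In Statistical Analysis, assign primary outcome 2 to a between-arm test: an arm-by-time term, or the arm effect on the change or on the second scan adjusted for the first, with a 95% CI. Settle in the same edit whether the measure is activation (Outcome Measures) or resting connectivity (Abstract).
2. State that an acupuncture effect will be claimed only from that estimate.
3. Keep the paired t tests as description within each arm, and state that significance in verum without significance in sham is not evidence of a difference.
4. Reword the second clause of the main hypothesis as a verum-sham difference in change.

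The cost is wording and one analysis of data already being collected. The downside is fewer significant before/after results. The between-arm test is also demanding at this size: at two-sided 5% and 80% power the detectable difference is 1.06 SD of the change score with 15 per arm and 0.74 SD with 30 per arm.

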## Methods

### Trial Design, Setting, and Aim

This study will be a single-center, block-randomized, placebo-controlled, parallel-group clinical trial. The study will be conducted at the College of Korean Medicine at Sangji University. This protocol complies with the SPIRIT (Standard Protocol Items: Recommendations for Interventional Trials) guidelines [25]. The aim of this study is to investigate the acute neural mechanisms of acupuncture stimulation concerning CR and to identify the neural substrates of CR in the group without cognitive impairment and the group with cognitive impairment using fNIRS.

The participants will be divided into 2 equal groups: the verum acupuncture group (study group) and the sham acupuncture group (control group). After each group is confirmed to participate in the study through screening (visit 0), fNIRS scanning and acupuncture manipulation will be conducted at visit 1. Cognitive function assessments, including the Korean version of the Mini-Mental State Examination (MMSE-K) and Montreal Cognitive Assessment (K-MoCA), will be conducted during screening. At visit 1, each participant will be measured twice using fNIRS (first and second scan) before and after acupuncture stimulation. Finally, CR marker assessment, such as the Cognitive Reserve Index Questionnaire (CRIq), will be conducted through interviews in visit 1. The period between visit 0 and visit 1 will not exceed 1 week. Participant recruitment was initiated on August 22, 2023, and the study is scheduled to continue until February 2025. The flow chart is illustrated in Figure 1, and the overall procedure is presented in Table 1.

